## Abstract

Posttraumatic stress disorder (PTSD) and substance use disorders (SUDs) often co-occur and are associated with a more severe clinical profile than either disorder alone. Prolonged Exposure (PE) is empirically supported treatment for PTSD and has demonstrated effectiveness among those with a co-occurring SUD. However, PE is not typically offered in substance use treatment settings, in part due to concerns about feasibility, retention, and symptom exacerbation, as well as structural misfit with time-limited residential and outpatient programs. Massed Prolonged Exposure (M-PE), PE delivered multiple times per week and completed within a condensed timeframe, yields comparable treatment outcomes to PE and may better align with the structure of residential and outpatient care and address key barriers to implementation. Here, we describe an ongoing randomized controlled trial investigating the efficacy of M-PE versus trauma treatment as usual (TAU) delivered concurrent to SUD TAU, among individuals with co-occurring PTSD and substance use disorders enrolled in a comprehensive residential and outpatient SUD program. In addition to examining treatment outcomes, this trial utilizes qualitative methods to gain a deeper understanding of participants’ experiences and evaluate M-PE implementation barriers and facilitators in an SUD treatment setting. We describe the development and implementation of this randomized clinical trial.

## Introduction

1

Posttraumatic stress disorder (PTSD) and substance use disorders (SUDs) frequently co-occur with more than 40% of individuals with PTSD meeting criteria for an SUD and 35% of those with an SUD meeting criteria for PTSD [[1], [2], [3]]. PTSD + SUD is associated with worse clinical outcomes than either disorder alone and these individuals have higher rates of additional comorbid psychiatric diagnoses, higher rates of suicide attempts, and greater functional impairment across social, vocational, and health domains [1,2,[4], [5], [6], [7], [8], [9], [10], [11]].

Prolonged Exposure (PE) has demonstrated effectiveness in the treatment of PTSD + SUD [12,13]. PE is a gold-standard trauma-focused intervention for PTSD that addresses trauma-related avoidance and cognitions (e.g., “I cannot trust anyone,” “the world is completely unsafe”) through use of imaginal and in-vivo exposures [14,15]. To date, there have been more than 20 clinical trials supporting the efficacy and effectiveness of PE [4]. These trials have resulted in large effect sizes with nearly three-quarters of individuals demonstrating treatment gains and 40% no longer meeting PTSD criteria by the end of treatment. Among those with PTSD + SUD, PE is more effective in reducing PTSD symptoms than SUD-only treatment and more effective than non-trauma-focused interventions for PTSD + SUD [[16], [17], [18], [19]]. Importantly, PE is well-tolerated among this population with no indication that PE results in higher rates of relapse, substance use, or symptom severity compared to treatment as usual (TAU) [12,13,20].

Despite increasing empirical support for PE among PTSD + SUD populations, PE is not typically offered in SUD treatment settings. This gap is likely driven by multiple influences including clinician beliefs regarding patients’ ability to manage exposure therapy and programmatic barriers such as poor retention and high patient dropout rates [16,21,22]. Further, PE is typically offered as 12 weekly individual sessions; however, many SUD treatment settings are time-limited (e.g., 30-, 60-, or 90-day residential and intensive outpatient programs) which may not align with a typical PE schedule. Residential and comprehensive outpatient (outpatient settings offering multiple individual/group therapy sessions per week in addition to medical, social, and/or family support) settings could serve as an opportunity to increase access to trauma-focused care as comprehensive outpatient formats are associated with higher rates of treatment attendance and completion rates [[23], [24], [25], [26]]. PTSD treatment offered through comprehensive outpatient programs is associated with lower dropout rates and longer abstinence periods [27,28]. Modifying PE to fit outpatient and residential SUD contexts could lead to enhanced treatment outcomes and greater access to care for those with PTSD + SUD.

One such modification is to offer PE in massed format. Massed PE (M-PE) offers sessions 3-5 times per week such that patients can complete treatment in 2-5 weeks as opposed to 3-5 months. There is growing support for M-PE with M-PE demonstrating higher retention, lower treatment dropout, higher session attendance, and similar treatment gains compared to weekly PE [[29], [30], [31]]. Further, offering M-PE in residential and comprehensive outpatient programs has the potential to expand access to trauma-focused care for individuals who might otherwise be unable to engage in standard outpatient PE as these programs are designed to provide frequent, structured treatment contact, often five or more days per week in residential care and up to five days per week in comprehensive outpatient care. Pilot work has shown M-PE to be feasible and acceptable in comprehensive outpatient settings with pilot work demonstrating lower dropout and greater PTSD and depression symptom reductions compared to treatment as usual (TAU) at 3-month follow-up [23].

The current study aims to expand upon this work as the first randomized hybrid Type I efficacy/effectiveness clinical trial of M-PE in a residential and comprehensive outpatient SUD treatment facility. This trial will compare M-PE + SUD TAU to trauma TAU + SUD TAU (henceforth M-PE v. TAU) among individuals with PTSD + SUD at an SUD treatment facility in the Southeastern United States. We will assess changes in PTSD symptoms, substance use outcomes (e.g., number of use days, substance-related problems), depressive symptoms, suicidal ideation, and quality of life among 168 patients enrolled in a residential or comprehensive outpatient SUD program. Further, we aim to assess potential treatment outcome moderators and mediators such as reductions in substance craving and trauma-related cognitions [[32], [33], [34], [35]]. A mixed-methods approach including qualitative interviews of participants, study therapists, and study site staff will be used to evaluate the implementation and acceptability of M-PE within the SUD program.

## Design and methods

2

We are currently conducting a randomized (two condition) single center ([blinded for review]) controlled trial of M-PE v. TAU for individuals with PTSD enrolled in a community SUD treatment program. Following a baseline assessment confirming diagnoses of PTSD and an SUD, participants are randomized via REDCap to receive TAU or M-PE. In addition to the treatment protocol, qualitative interviews will be conducted with a purposive sample of treatment site staff and study participants. The study was approved by the Institutional Review Board of [blinded for review] and is registered at ClinicalTrials.gov (NCT06968832).

### Participants

2.1

#### Intervention participants

2.1.1

Projected enrollment is 168 individuals with PTSD + SUD over five years with approximately equal disruption between sex. Potential participants are identified through electronic medical records, mental health intakes, and/or referrals by providers at [site]. Participants are recruited from the residential and comprehensive outpatient programs and pre-screened for eligibility by the treatment site study coordinator. Inclusion criteria are as follows: 1) 18+ years old; 2) have full or subthreshold (missing no more than one symptom on clusters B, C, D, or E) DSM-5 PTSD; and 3) able to give informed consent. Exclusion criteria are as follows: 1) impaired mental status, 2) significant current risk of suicidal/homicidal behavior, 3) unmanaged psychotic or bipolar disorder, or 4) refusal to be audio-recorded. Given the length of study participation and the high rates of comorbid medical and mental health conditions with PTSD and SUD, individuals may receive other medical and mental health care (e.g., support groups, family therapy, psychiatric medications) while participating in the study. Individuals consent to baseline assessment and those who are eligible are consented to treatment prior to randomization.

#### Qualitative interviews

2.1.2

Prior to study enrollment, staff members at the intervention site (*n* = 15) were invited to complete individual qualitative interviews co-produced by a Community Advisory Board to 1) capture experiences prior to study onset and 2) identify any potential gaps in the study protocol prior to implementation (e.g., therapist scheduling needs, participant transportation needs). To capture a variety of roles and expertise, all members at the treatment site were invited to participate. To maintain anonymity and avoid coercion, interested participants contacted an external research coordinator to schedule interviews and all interviews were conducted by study staff unaffiliated with the treatment site. Members of the study team from the treatment site were not provided information about qualitative interview participants. Following study completion, these individuals, along with all study therapists, will be invited to participate in a follow-up interview.

A second series of qualitative interviews will be conducted with research participants. A subset of participants randomized to a treatment condition will be randomly selected and invited to participate in a qualitative interview following the end-of-treatment interview window. We anticipate interviewing approximately 12 to 15 participants from each condition or until saturation is met (*n* = 24 – 30). Participants will be eligible regardless of treatment completion status in order to capture a wide range of experiences (e.g., reasons for terminating study participation). Interviews will be conducted by research team members not affiliated with the treatment site.

### Treatment

2.2

Eligible participants are randomly assigned to TAU or M-PE with randomization stratified by residential or outpatient treatment using randomly permuted-blocks with equivalent allocation to each treatment group. Randomization will be computer-generated with all clinical assessors blinded to treatment condition. Individual conditions are described below. For both TAU and M-PE, potential substance use during treatment is managed on a case-by-case basis by treatment site staff and decisions are made independently of this study.

#### Treatment as usual (TAU)

2.2.1

The treatment site offers comprehensive care including detoxification, residential and outpatient programs, and recovery housing. Typical length of stay in residential care is approximately 30 to 90 days tailored to individual need. Patients in the residential program engage in care from 7:30am to 5:00pm Monday through Friday with optional programming on weekends and evenings. Typical length of comprehensive outpatient participation is person-centered with length of participation contingent upon individual need. Individuals in the outpatient program participate in group and individual therapy up to 3 days per week depending on need. Providers at the treatment site come from multidisciplinary backgrounds including licensed social workers, Master's and doctoral level clinicians, licensed marriage and family counselors, and nurse practitioners.

**SUD TAU.** Services are tailored to the patient and include individual and group therapy, 12 steps groups, family counseling, medication management, and social support services that implement a variety of evidence-based approaches such as motivational interviewing and cognitive behavioral therapy.

**Trauma TAU.** Participants engage in a resiliency, skills-based group based on adaptations of the Seeking Safety curriculum and comprised of five 90-min standalone sessions. These sessions focus on development of coping skills and symptom management without exposure to the traumatic event.

#### Massed prolonged exposure (M-PE)

2.2.2

M-PE follows the structure of PE and includes the following components: 1) breathing retraining, 2) imaginal exposure to the traumatic event, and 3) in-vivo exposures to trauma-related avoided situations. Outside of sessions, participants practice in vivo exposures and listen to session recordings. M-PE is delivered in 60-min sessions 3-4 times per week for 12-16 sessions as indicated by participant needs. Those randomized to M-PE participate in all TAU activities in addition to meeting with their individual M-PE counselor during free periods during typical treatment hours (7:30am to 5:00pm). M-PE is delivered by treatment site providers and research therapists including Master's level therapists and licensed social workers. M-PE providers receive twice weekly supervision by a licensed, Ph.D.-level clinical psychologist and all intervention procedures are overseen by the two study principal investigators.

### Assessments

2.3

Participants complete a baseline interview prior to treatment randomization to establish diagnoses and symptom presentation in addition to interviews at the end-of-treatment (approximately 6 weeks post-randomization) and 1-, 3-, and 6-months post-treatment. Brief self-report assessments are administered 2-3 times per week throughout the treatment course. Participants are compensated for interviews but not for treatment sessions. All assessments are administered by experienced, blinded examiners at the Master's or doctoral-level with a minimum inter-rater reliability of .80 on PTSD and SUD clinical interviews. To determine inter-rater reliability over the study course, 10% of interviews will be randomly selected to be independently scored by licensed, Ph.D.-level researchers. Assessments include a combination of diagnostic interviews and self-report measures. The primary outcomes of interest are changes in PTSD symptoms, substance use frequency and problems, depressive symptoms, and quality of life. Additional focal assessments include measures of trauma-related cognitions and substance use craving. See Table 1 for the assessment schedule.

**Table 1 tbl1:** Patient assessment schedule.

Measure	Purpose	Format	Pretreatment	During Treatment	At End of Treatment	1-, 3-, 6 Month Post-treatment
P-4 Suicide Severity Rating Scale	Eligibility, secondary outcome	Interview	X	-	X	X
Structured Clinical Interview for DSM-5	Characterize Sample	Interview	X	-	-	-
Clinician Administered PTSD Scale-5	Eligibility, Primary Outcome	Interview	X	-	X	X
Timeline Follow Back Interview	Primary Outcome	Interview	X	-	X	X
PTSD Checklist –DSM-5	Secondary Outcome, Mediator, Within Treatment Change	Self-Report	X	X	X	X
Short Inventory of Problems Revised (SIP-R)	Primary Outcome	Self-Report	X		X	X
Substance Use Inventory (SUI)	Secondary Outcome, Within Treatment Change	Self-Report	X	X		
Patient Health Questionnaire-9	Secondary Outcome	Self-Report	X	-	X	X
Brief Inventory of Psychosocial Functioning	Secondary Outcome	Self-Report	X	-	X	X
WHO – Disability Assessment Schedule	Secondary Outcome	Self-Report	X	-	X	X
Brief Substance Craving Scale	Secondary Outcome, Within Treatment Change	Self-Report	X	X	X	X
Posttraumatic Cognitions Inventory	Mediator		X	X	X	X
Treatment Services Review	Characterize Sample, Potential Covariate	Interview	-	-	X	X
Demographic Questionnaire	Characterize Sample, Moderator	Self-Report	X	-	-	-

#### Assessor administered measures: baseline and follow-up interviews

2.3.1

**PTSD Diagnostic Interview**. The clinician-administered PTSD Scale for DSM 5 (CAPS-5) [36] is the primary PTSD symptom measure. At baseline, the CAPS-5 is used to determine presence of PTSD and pre-treatment PTSD severity. Items are rated on both frequency and intensity to derive a severity score for each symptom ranging from 0 (absent) to 4 (extreme). Items scored at a severity of 2 (moderate) or higher are considered “present” and counted toward the total number of symptoms required for each DSM-5 symptom cluster. DSM-5 requires presence of 1 or more re-experiencing symptoms (cluster B), 1 or more avoidance symptoms (cluster C), 2 or more alterations in cognition or mood symptoms (cluster D), and 2 or more arousal symptoms (cluster E). The present study allows individuals to be subthreshold by 1 symptom. The CAPS-5 also assesses dissociation symptoms, social and occupational functioning, and response validity.

**Substance Use Interviews**. The Structured Clinical Interview for DSM-5 (SCID) [37] is used to assess for presence of SUD(s) at baseline. The Timeline-Follow back (TLFB) [38] is used to assess frequency of substance use and percent of substance use days. At baseline, the TLFB assesses the 90 days prior to baseline. Subsequent interviews assess the period between the last assessment and the current interview date to allow for coverage of all days of the study period. During the TLFB, participants note any dates in which they were in a controlled environment (e.g., residential care, detoxification, hospitalization, incarceration).

**Additional Interview Measures**. Suicidal ideation is assessed using the P4 [39]. This interview assesses current suicidal ideation, plans, and intent as well as history of suicidal thoughts and behaviors. The Treatment Services Review (TSR) [40] assesses participation in various interventions (e.g., individual therapy, residential treatment, detoxification, psychopharmacological intervention) as a total count of times each service was received since the last interview.

#### Self-report measures: baseline and follow-up surveys

2.3.2

**PTSD Measures.** The PTSD Checklist for DSM-5 (PCL-5) [41,42] is a 20-item self-report measure capturing DSM-5 PTSD Criterion B-E. Items are rated on a 1 to 5 scale with higher scores indicating greater PTSD symptom severity. The Posttraumatic Cognitions Inventory (PTCI) [43] is a 39-item self-report measure capturing cognitions related to traumatic event exposure. Items are rated on a 1 to 7 scale with higher values indicating greater negative cognitions.

**Substance Use Measures.** The Brief Craving Scale (BCS) [44] is a 16-item measure assessing current craving intensity and frequency. The Short Inventory of Problems Revised (SIP-R) [45] is a 17-item measure assessing substance use frequency and associated problems. Items are rated on a 1 to 4 scale with higher values indicating more substance-related problems. The Substance Use Inventory (SUI) [46] is a 7-item measure capturing the quantity and frequency of alcohol and substance since last assessment.

**Treatment Satisfaction.** At the end-of-treatment assessment, participants complete the Client Satisfaction Questionnaire (CSQ-8) [47]. This 8-item self-report measure assesses participant satisfaction with services provided. Items are rated on a 1 to 4 scale with greater values indicating greater satisfaction.

**Additional Measures.** Demographic characteristics are captured at baseline. Depressive symptoms are assessed using the 9-item Patient Health Questionnaire (PHQ-9) [48]. This measure captures depressive symptoms on a 0 to 3 scale with higher scores indicating greater depressive symptoms. The Brief Inventory of Psychosocial Functioning (BIPF) [49,50] is used to assess quality of life and functional impairment. This measure contains seven items rated on a 1 to 7 scale with higher values indicating greater psychosocial impairment. The WHO Disability Schedule 2.0 (WHODAS) [51] is used to assess functional impairment. This 12-item measure assesses impairment in cognition, mobility, self-care, getting along, life activities, and daily life participation.

#### Self-report measures: in-treatment surveys

2.3.3

In-treatment self-report assessments include the PCL-5, PTCI, BCS, and SUI. This assessment takes approximately 10-15 min to complete. For those randomized to M-PE, in-treatment assessments occur prior to each M-PE session. For participants randomized to TAU, in-treatment assessments are administered twice weekly over 6 weeks to reflect the M-PE survey schedule.

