Despite these notable strengths, this study does have limitations. M-PE is designed to include 3-5 sessions per week. Though this structure works well in residential and comprehensive outpatient settings, it may be less feasible for those in outpatient SUD settings. Further, the limited inclusion/exclusion criteria is meant to enhance generalizability but also introduces potential confounds associated with co-morbid diagnoses (e.g., depression, anxiety, medical comorbidities) common in PTSD + SUD populations [66,67]. We also allow participants to engage in ongoing treatments for physical and mental health conditions which may confound treatment outcomes. Lastly, we anticipate we may see difficulties with attendance and treatment continuation as participants transition from residential to outpatient care. To address this, we have included frequent reminder calls from study staff regarding appointments, flexible treatment scheduling and assessment date ranges, and options for study-funded transportation (e.g., bus vouchers, ride shares).

There is strong empirical support for including trauma-focused interventions, such as PE, into SUD care [1,2,12]. M-PE has shown increased treatment attendance, decreased dropout, and comparable treatment outcomes to weekly PE [23,[29], [30], [31]]. This massed format may better fit the structure of residential and comprehensive outpatient SUD programming as the massed format allows for treatment completion within 3-5 weeks. This study will provide evidence as to whether the inclusion of M-PE to TAU in an SUD program enhances treatment and quality of life outcomes. Further, qualitative interviews will provide valuable information for the implementation and feasibility of M-PE in SUD care from the perspective of participants, providers, and administrators.

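### In-treatment surveys follow sessions in M-PE but the calendar in TAU, so the Substance Use Inventory has different recall windows by arm and, in M-PE, stops when sessions stop

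*Protocol article*

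**What the plan says.** Section 2.3.3 gives each arm its own rule for the in-treatment PCL-5, PTCI, craving scale and SUI. For the experimental arm: "For those randomized to M-PE, in-treatment assessments occur prior to each M-PE session". For the control arm: "For participants randomized to TAU, in-treatment assessments are administered twice weekly over 6 weeks to reflect the M-PE survey schedule".

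The M-PE session plan is in section 2.2.2: "M-PE is delivered in 60-min sessions 3-4 times per week for 12-16 sessions as indicated by participant needs". The Discussion gives a similar duration: "the massed format allows for treatment completion within 3-5 weeks". Section 2.3 states one survey frequency without separating the arms: "Brief self-report assessments are administered 2-3 times per week throughout the treatment course".

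Section 2.3.2 says that the SUI "is a 7-item measure capturing the quantity and frequency of alcohol and substance since last assessment". Table 1 lists its purpose as "Secondary Outcome, Within Treatment Change" and marks it at pretreatment and during treatment only. The PCL-5, PTCI and craving scale are also marked at end of treatment and at the 1-, 3- and 6-month visits.

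**The concern.** The control schedule is described as mirroring the M-PE one, but it differs in trigger (calendar against session), in span and, at the planned pace, in spacing. The survey frequency in section 2.3 also disagrees with 3-4 sessions per week, each preceded by a survey.

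For most instruments this is a modest nuisance. For the SUI the survey interval is the measurement window, so a different interval means a different quantity is recorded. A per-day score would correct window length but would not supply the weeks in which M-PE has no SUI.

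Those weeks need not resemble the ones observed. Section 2.2.1 puts residential stays at roughly 30 to 90 days, so some discharges can fall inside the 42 days surveyed in TAU but after M-PE surveys have ended. The Discussion expects trouble at that transition: "we anticipate we may see difficulties with attendance and treatment continuation as participants transition from residential to outpatient care". In M-PE a participant who stops attending also stops being measured on the SUI; in TAU the surveys continue. If the within-arm imputation of section 2.8.2 were applied to the SUI, participants finishing on schedule would supply no M-PE data from the later weeks.

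**Working it through.** **Inputs.** M-PE: 3-4 sessions per week, 12-16 sessions (section 2.2.2), one survey before each (section 2.3.3). TAU: 2 surveys per week for 6 weeks (section 2.3.3), which is 2 × 6 = 12 surveys over 42 days. Residential stay: 30 to 90 days (section 2.2.1).

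**The article's own duration.** Course length = sessions / sessions per week: 12/4 = 3.0, 12/3 = 4.0, 16/4 = 4.0 and 16/3 = 5.33 weeks. This agrees closely with the 3-5 weeks in the Discussion.

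**Windows and coverage.** Mean window = 7 / surveys per week. The middle column allows for a slower pace, with the same sessions spread over 6 weeks.

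| | M-PE, planned pace | M-PE, spread over 6 weeks | TAU |
|---|---|---|---|
| Surveys per week | 3 to 4 | 12/6 = 2.0 to 16/6 = 2.67 | 2 |
| Mean window, days | 7/4 = 1.75 to 7/3 = 2.33 | 16 sessions: 2.625; 12 sessions: 3.5 | 7/2 = 3.5 |
| TAU window / M-PE window | 1.5 to 2.0 | 1.0 to 1.33 | - |
| Days covered of 42 | 21 to 37.3 | about 42 | 42 |
| Days uncovered | 4.7 to 21 | about 0 | 0 |

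At the planned pace, 2 × (6 − 5.33) = 1.3 to 2 × (6 − 3) = 6 of the 12 TAU surveys fall after the last M-PE survey.

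**Dropout (assumed example: stopping after 4 sessions).** At 4 per week, 7 days are covered and 35 are not. At a slower 2 per week, 14 are covered and 28 are not.

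**What this does to a comparison, with equal true use in both arms.** Each line is conditional on a scoring rule that the article does not state.

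- Raw use days per report: 1.75/3.5 = 0.50 to 2.33/3.5 = 0.67, so M-PE reads 33-50% lower at the planned pace. If sessions are spread, 2.625/3.5 = 0.75 to 1.00, so 0-25% lower.
- Any use per report, assuming a 10% daily chance of use: 1 − 0.9^1.75 = 16.8% to 1 − 0.9^2.33 = 21.8% in M-PE, against 1 − 0.9^3.5 = 30.8% in TAU.
- Summed over treatment at the planned pace: 21/42 = 50% to 37.3/42 = 89% of the TAU total.
- Per day covered: the window effect disappears, but the calendar periods still differ. Assume a 30-day stay starting at randomisation and daily use after discharge r times that before. Mean relative daily use to day T is [min(T, 30) + r × max(0, T − 30)] / T. With r = 2, TAU (T = 42) is 54/42 = 1.286; M-PE is 1.0 at T = 21 and 1.196 at T = 37.3, so M-PE reads 22% to 7% lower. With r = 0.5, TAU is 0.857 and M-PE is 1.0 or 0.902, so M-PE reads 17% to 5% higher. With r = 1 or a 90-day stay the effect is nil.

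**The case against.** The strongest reply is that no planned analysis is shown to be harmed. How the SUI is scored, and whether exposure is adjusted for, can properly be left to the analysis plan. That stands. A reader might infer that the trial will report substance use 33-50% too low in M-PE. The article does not support this, because it nowhere proposes comparing raw SUI reports between arms.

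A reader might also infer that the primary substance use result is compromised. It is not. The TLFB covers every day of the study in both arms, is given by blinded assessors and records dates in controlled environments (section 2.3.1). Use on the uncovered days is therefore recorded, though not by the SUI.

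Pace matters too. Twelve sessions over 6 weeks would reproduce the TAU schedule, and missed sessions or a late start could bring M-PE close to it. The number of surveys is already similar (12 against 12-16). This is why the range starts at about zero. It does not remove the dependence of measurement on attendance in one arm only.

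Finally, the absence of an end-of-treatment SUI rests on blank cells in Table 1, where most unused cells carry a dash, and section 2.3.2 describes the SUI under a heading that includes follow-up surveys. If the SUI were given at end of treatment, its recall would span the gap for anyone assessed. But the SIP-R row leaves its during-treatment cell blank in the same way, so a blank most naturally means not given.

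**Conclusion.** The point holds as a flaw in a stated rule, limited to a secondary self-report measure. Followed as written, the two rules give the SUI windows of 1.75-2.33 days against 3.5 at the planned pace, and M-PE coverage that ends with the last attended session. Uncovered time is about 0 to 21 of 42 days for completers, and 28-35 days in the four-session dropout example.

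Neither the size nor the sign of a bias can be fixed from the article: both depend on scoring, on actual session pace and on how use changes after discharge. That M-PE surveys end at dropout is inferred from the session trigger, since no other M-PE survey rule is given. CAPS-5 is unaffected, as is the TLFB, and the PCL-5, PTCI and craving scale are also taken at common visits. A change is worth making because the trial is ongoing and an analysis plan can add an offset but cannot create SUI reports that were never collected.

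**What to change.** Keep the M-PE pre-session surveys, which are a reasonable way to follow change during treatment; nothing here requires replacing them. Then:

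1. After M-PE completion or dropout, continue the surveys twice weekly by calendar until week 6 from randomisation.
2. Give the SUI at the end-of-treatment visit in both arms and mark it in Table 1.
3. Record the date of every survey, and compare SUI use between arms per day covered (log of days as offset) over the same 6 calendar weeks.
4. For M-PE participants already past this point, show TLFB days for the uncovered weeks alongside the SUI.
5. In section 2.3, replace the single 2-3 per week figure with the frequency for each arm. In section 2.3.3, replace the statement that TAU mirrors M-PE with the actual rule: before each session in M-PE, then twice weekly to week 6; twice weekly to week 6 in TAU.

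The cost is small. In-treatment surveys in TAU are unchanged; the end-of-treatment visit gains the 7-item SUI in both arms. M-PE completers at the planned pace get about 1.3-6 more surveys of 10-15 minutes, or roughly 13 (1.3 × 10) to 90 (6 × 15) minutes in all. A participant who stops after four sessions would get 2 × (6 − 2) = 8 to 2 × (6 − 1) = 10, and some will not respond. Self-report data already enter Qualtrics through participant links (section 2.8.1), so no new system is needed. SUI coverage for M-PE participants treated before the change will remain incomplete and should be reported as such.
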